#### Where is Waldo

An illustration of Martin Handford’s “Where is Waldo?” is presented on a DIN A3 sheet of paper. The picture contains dozens or more people doing a variety of things in a particular place. The patient has to find some specific signs or objects listed on a sheet of paper by marking them with a pen on the DIN A3 sheet within 5 min. This task is mainly intended to train selective attention and working memory and was created by our group.

#### Planning

In the last task, the patient must read a text in which an imaginary person has to perform transactions or organize appointments. The patient’s task is to solve the problems by writing down a concrete solution. The time limit for this task is 10 min. The task is mainly intended to train planning ability and working memory and was adapted from Müller et al. (2013) [37].

### Planned statistical analyses

The effect of cognitive training will be analyzed by repeated measures (mixed between-within) analysis of variance (ANOVA) with groups (control group/intervention group) as the between-subject factor and assessment time (baseline and all follow-up assessments) as the within-subject factor for all cognitive tests and questionnaires, respectively. Assumptions for repeated measures ANOVA will be tested using the Levene test for variance-homogeneity and Mauchly’s test for sphericity. If sphericity is violated, alpha levels will be adjusted using the Greenhouse-Geisser correction. Normal distribution will be tested using the Shapiro-Wilk test. To control for the possibility of confounder variables that could affect the results, we will conduct additional repeated measures analysis of covariance (ANCOVA), which includes covariates such as preoperative cognitive values, age, sex, education, psychiatric scores (depression/anxiety), and perioperative variables such as duration of extracorporeal circulation, administration of anesthesia, and number and size of ischemic lesions.

Post hoc explorative between-subject comparisons will be analyzed using the *t* test for independent samples. In this case, we will compare the intervention group with the control group by calculating a change score in cognitive values (post-training score minus pre-training score). The change in cognitive values is the dependent variable, and the treatment group (cognitive training group/control group) is the independent variable.

Within-subject comparisons will be analyzed using the paired *t* test. When the assumptions for parametric tests (normal distribution, variance-homogeneity between two groups) are not given, the variables will be analyzed using non-parametric variance techniques. In this case, between-group differences will be calculated using the Mann-Whitney U test, using change scores in cognitive values (post-training score minus pre-training score) and the Wilcoxon signed-rank test for within-group comparisons. Nominal variables will be analyzed by Pearson’s chi-squared test. Depending on the parametric level of the data, correlation with continuous variables will be calculated using Pearson product-moment correlation, Spearman rank correlation, or Kendall tau correlation. Effect size of the cognitive training will be calculated by the difference in the pretest-posttest measure between the intervention and control group, weighted by the pooled standard deviation of the pretest measurement, because this is the recommended choice for a pretest-posttest controlled design [38]. The criterion for statistical significance will be set at *p* < 0.05. In the case of multiple tests, we will control *p* values using the false discovery rate (FDR) correction method [39]. Since we expect dropout of some patients on follow-up assessments, all patients will be included in the intention-to-treat analysis, where missing data will be imputed by a multiple imputation method. To evaluate the impact of missing data, a complete case analysis will also be performed, followed by best-worst and worst-best case sensitivity analyses.

Another approach to identifying a training effect on cognition will be to compare the frequencies of POCD and POCI between the groups using Pearson’s chi-squared test. POCD will be defined as a decline from pre to post assessment of 1 standard deviation in at least two neuropsychological parameters as this is a widely used method [2]. Similarly, POCI will be defined as an improvement from pre to post assessment of 1 standard deviation in at least two neuropsychological parameters.

Interim analyses will be carried out during the study period to identify adverse events, an overwhelming effect, or the futility of the experimental arm. In this case, the study could be terminated prior to its completion. The decision will be made by the study team.

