All patients will pass a detailed neuropsychological assessment the day before surgery, at discharge from rehabilitation, and at 3 and 12 months after discharge. At every time point, patients will complete a standardized questionnaire on depression and anxiety. Questions about cognitive failure in daily life and HQL will be assessed before heart surgery and at 3 and 12 months after discharge from rehabilitation. Before surgery, data documentation will include age, sex, education, body mass index, preexisting conditions, and medication. Documentation of perioperative date will be the type and amount of anesthesia administered, duration of anesthesia administration, type and amount of analgesia administered, duration of analgesia administration, duration of surgery, duration of extracorporeal circulation, cross-clamp time and perioperative complications. Post-surgery intensive care unit (ICU) days, total length of inpatient stay, postoperative complications and postoperative delirium will be recorded. At 6–10 days after surgery, MRI of the brain will be conducted to screen for cerebral ischemia, hemorrhage, or other acute pathologic conditions potentially confounding neuropsychological assessment and the effects of cognitive training. Following the inpatient stay in the acute hospital (approximately 7 days), patients will be directly transferred to the department of rehabilitation at the Kerckhoff Clinic in Bad Nauheim, Germany.

During their stay at the rehabilitation center, which usually lasts 3 weeks, all patients will receive standard cardiac rehabilitation including physical exercise, medical management and nutritional counseling. The cognitive training group will undergo an additional cognitive training program consisting of paper-and-pencil exercises. The study design is shown in Fig. 1. A detailed trial schedule in accordance with the Standard Protocol Items: Recommendation for Interventional Trials (SPIRIT) guideline is shown in Table 1.

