### Primary outcome measure

The primary outcome measure will be the training effect on all objectively measured neuropsychological functions at discharge from rehabilitation.

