### Secondary outcome measure

As a secondary outcome, we will evaluate the training effect of all objectively measured neuropsychological functions at 3 and 12 months after discharge from rehabilitation. Second, we will evaluate the training effect on the subjective self-assessment and external assessment by relatives of cognitive failures at 3 and 12 months after discharge from rehabilitation. Third, we will evaluate the training effect on HRQ at 3 and 12 months after discharge from rehabilitation. Fourth, we want to investigate the extent to which the cognitive training has an impact on depression at all follow-up time points. Last, we will examine the impact of perioperative cerebral ischemia on the neuropsychological measured training effect at all follow-up time points. Perioperative cerebral ischemia will be measured with postoperative DW-MRI during the first postoperative week. The number and size of ischemic lesions are determined and will be used as a control variable for the analysis of the training effect.

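### The primary outcome is the effect at discharge, but the main planned analysis tests for any group difference across all four visits and so does not answer that question

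*Protocol article*

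**What the plan says.** The Primary outcome measure section of the protocol article states: "The primary outcome measure will be the training effect on all objectively measured neuropsychological functions at discharge from rehabilitation". The end of the Background likewise places the primary evaluation directly after training. The Secondary outcome measure section puts the later visits in second rank: "As a secondary outcome, we will evaluate the training effect of all objectively measured neuropsychological functions at 3 and 12 months after discharge from rehabilitation".

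The Planned statistical analyses section then gives one model for everything: "The effect of cognitive training will be analyzed by repeated measures (mixed between-within) analysis of variance (ANOVA"), with group as the between-subject factor and "assessment time (baseline and all follow-up assessments) as the within-subject factor for all cognitive tests and questionnaires, respectively". Cognitive testing takes place "the day before surgery, at discharge from rehabilitation, and at 3 and 12 months after discharge", so for the cognitive tests the time factor has four levels.

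The same section adds a repeated measures ANCOVA, described as additional, "which includes covariates such as preoperative cognitive values". The two-group comparison of post-training minus pre-training scores is introduced with "Post hoc explorative between-subject comparisons will be analyzed using the" *t* test. The Mann-Whitney test on change scores applies only if parametric assumptions fail. The comparison of decline and improvement frequencies is offered as another approach. Missing data are multiply imputed for an intention-to-treat analysis of all patients, and complete-case and extreme-case analyses serve as sensitivity checks.

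**The concern.** The repeated measures ANOVA is the only analysis of the training effect that is not labelled additional, exploratory, a fallback or an alternative approach. In such a model the training effect is carried by the group-by-time term. With four visits that term is a 3-degree-of-freedom test of whether the two groups' profiles differ anywhere. It mixes the primary time point with two secondary ones and does not estimate the effect at discharge.

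Two consequences follow. First, a significant main analysis could reflect only a 3- or 12-month difference yet be reported as success on the primary outcome. Second, the comparison that does address the primary question has exploratory status. If the authors rely on it after seeing the data, it is post hoc by the plan's own label. In addition, a question that can be answered at discharge is made to lean on visits with much heavier dropout.

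**Working it through.** **Inputs from the Power and sample size estimation section.** η² = 0.10; 37 evaluable per group; 80% power; two-sided 0.05; 20% dropout between each of the four assessments; 72 recruited per group.

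**1. Reproducing the plan's figures.**
- f = √(0.10/0.90) = 0.333, so d = 2f = 0.667.
- A two-sided two-group *t* test has power 79.7% at 36 per group and 80.8% at 37, which gives the stated 37.
- Inflation for three intervals: 37/0.8³ = 72.3, stated as 72.

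Both figures reproduce. The 37 is therefore the number expected to remain at 12 months.

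**2. Can the main test be positive with nothing at discharge?** Assumptions that the document does not give: compound symmetry with correlation ρ, complete data, no multiplicity correction, and an effect of 0.667 SD of the change score at 12 months only.
- With unit variance at each visit, the change score has SD √(2(1−ρ)), so δ = 0.667·√(2(1−ρ)).
- With one of four visits shifted, the sum of squared deviations of the group-difference profile is δ²(1 − 1/4) = 0.75δ².
- Noncentrality: λ = (n/2)·0.75·δ²/(1−ρ). Since δ²/(1−ρ) = 2 × 0.4444 = 0.889, ρ cancels. At n = 37, λ = 18.5 × 0.75 × 0.889 = 12.33.
- Degrees of freedom are 3 and 3(2 × 37 − 2) = 216, and the critical F is 2.65.
- Power of the group-by-time test is **84.4%**.

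A simulation with the Greenhouse-Geisser correction (2,000 trials per setting) agrees:

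| True effect, 37 per group | Group-by-time, four visits | Discharge minus baseline *t* test |
|---|---|---|
| None at any visit | about 5% | about 5% |
| 12 months only | about 85% | about 5% |
| 3 and 12 months only | about 93% | about 5% |
| Discharge only | about 84% | about 81% |

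Results are similar for ρ = 0.5 and ρ = 0.7.

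**3. How far does the main test rest on late visits?** Expected observed patients per group are 72 at baseline, 72 × 0.8 = 57.6 at discharge, 72 × 0.8² = 46.1 at 3 months and 72 × 0.8³ = 36.9 at 12 months. The missing share is 20% at discharge and 1 − 0.8³ = 49% at 12 months. Under multiple imputation, about half of the 12-month values in the four-visit test would be imputed.

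**4. Precision of a baseline-adjusted comparison.** With equal variances and pre-post correlation r, the variance of the ANCOVA estimate relative to the change-score estimate is (1 − r²)/(2(1 − r)) = (1 + r)/2. This is 0.65 at r = 0.3, 0.75 at 0.5, 0.85 at 0.7 and 0.90 at 0.8, so the variance is 10 to 35% lower over that range. The document gives no value for r.

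**The case against.** The strongest reply is that the ANOVA sentence is a generic description covering cognitive tests and questionnaires together. Three of the questionnaires (both cognitive failures questionnaires and the SF36) are not even given at discharge. The words confirmatory, interaction and omnibus do not appear in it. A mixed ANOVA permits a discharge contrast, a condensed article may leave that contrast to a fuller plan, and a post-minus-pre group comparison and a pretest-posttest effect size are both planned. A purely late difference would therefore probably be noticed. Some of this stands: the discharge comparison is not absent. But the article itself fixes the time levels and itself labels that comparison exploratory. This is a stated choice rather than a detail left out, and the effect size is an estimate, not a test.

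Four stronger readings are tempting, and the document does not support them.

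- *Patients without all four visits are dropped, so power falls from 94% (57 per group) to about 80% (37 per group).* Missing data are imputed for all patients in the main analysis. The lower figure describes only the complete-case sensitivity analysis.
- *The four-visit test is weak for a discharge effect.* For a discharge-only effect it has about 84% power against about 81% for the contrast.
- *The test produces too many false positives.* When there is no effect at any visit it rejects in about 5% of trials. Rejecting for a real late effect is not an error of the test; it answers a different question.
- *The ANCOVA is invalid because the preoperative score is both covariate and response.* The article does not say that baseline remains a response level in that additional analysis. If it did, simulated type I error would be 5.0 to 6.0%, which is not a material inflation.

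The 84% illustration is also a deliberately clean case: no effect straight after training and a full-size effect only at 12 months. It shows that the test does not isolate discharge. It does not forecast the trial's result.

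**Conclusion.** The concern holds as a mismatch between the primary question and the main test. Followed as written, the only analysis of the training effect without a subordinate label can be significant when there is no effect at discharge, while the comparison that addresses the primary outcome is exploratory. The size, about 84% against about 5% at 37 per group, rests on compound symmetry, complete data, no false discovery rate correction and an effect of 0.667 SD of change at 12 months only. The reliance on late data (49% of 12-month values missing against 20% at discharge) follows from the plan's own dropout rate. That the group-by-time term carries the training effect is an inference from the model, since the article does not name the term.

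**What to change.** In Planned statistical analyses, name the primary analysis for each cognitive measure as the between-group comparison at discharge adjusted for the preoperative score. This can be an ANCOVA of the discharge score, or the discharge contrast of a mixed model with baseline as covariate and the three follow-up visits as responses. Keep the planned false discovery rate control and multiple imputation. Make the 3- and 12-month contrasts and the all-visit ANOVA secondary. Wherever the preoperative score is a covariate, state that it is not also a level of the response.

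The cost is a few sentences of analysis text. No new data are needed, and 72 per group is enough: the expected 57 or so per group at discharge give about 94% power for a single two-group test at d = 0.667, before multiplicity correction. The change should be made before any unblinded analysis, because choosing the discharge contrast afterwards would be post hoc.

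### The adjusted repeated measures model uses the preoperative score both as an outcome level and as a covariate, so its group main effect is three quarters of the mean follow-up effect

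*Protocol article*

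**What the plan says.** All statements are in the Protocol article.

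- **Visits (Study design and enrollment).** Patients are tested at four points: "the day before surgery, at discharge from rehabilitation, and at 3 and 12 months after discharge".
- **Main model (Planned statistical analyses).** A mixed between-within ANOVA has group as the between-subject factor and "assessment time (baseline and all follow-up assessments) as the within-subject factor for all cognitive tests and questionnaires, respectively". Baseline is therefore an outcome level.
- **Adjusted model (same section).** To deal with confounders, the section adds an "additional repeated measures analysis of covariance (ANCOVA), which includes covariates such as preoperative cognitive values"; depression and anxiety scores are also listed. The levels of the time factor are not restated for this model.
- **Primary outcome (Primary outcome measure).** It is "the training effect on all objectively measured neuropsychological functions at discharge from rehabilitation".
- **Depression (Secondary outcome measure).** "we want to investigate the extent to which the cognitive training has an impact on depression at all follow-up time points". The HADS is collected at every visit.

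The article does not say which term of the ANCOVA is to be read as the adjusted training effect.

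**The concern.** In a baseline-adjusted analysis the preoperative score belongs on one side of the model only. Here it is an outcome at the first time level and also a predictor of that outcome. Given itself, the baseline score has no residual and no group difference. A group main effect averaged over four levels then contains one artificial zero.

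This ANCOVA is the article's only covariate-adjusted estimate of the training effect. A reader who takes its group term, or the difference between its adjusted group means, as the size of the benefit would report a figure that is too small for a purely mechanical reason. It would also disagree with the effect size defined later in the same section, which is the between-group difference in pre-to-post change divided by the pooled pretest SD and has no such dilution.

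**Working it through.** **Inputs from the article.** Four assessments (one baseline, three follow-ups); 1:1 allocation; 37 analysable patients per group; two-sided 0.05; planning effect η² = 0.10.

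**Assumptions, not in the article.** Complete data, normal errors, equal correlation between visits of 0.3 to 0.85, and illustrative effects between 0 and 0.5 SD.

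**The plan's own figure.** f = √(0.10/0.90) = 0.333, so d = 2f = 0.667. The noncentral t test gives power 0.797 with 36 per group and 0.808 with 37, so 37 is reproduced. With three intervals of 20% dropout, 37/0.8³ = 72.3, against 72 stated; 72 × 0.512 = 36.9. The sample size is not in question here.

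**Step 1: the coefficient.** Let b be the preoperative score and y₁, y₂, y₃ the follow-up scores. The between-subject part of the four-level model regresses the patient mean (b + y₁ + y₂ + y₃)/4 on group, b and any other covariates. Least squares is linear in the outcome, so

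adjusted group effect = (β_b + d₁ + d₂ + d₃)/4,

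where d₁, d₂, d₃ are the baseline-adjusted group differences at the follow-ups and β_b is the group coefficient when b itself is the outcome. Because b is also a predictor, β_b = 0 exactly. Hence

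adjusted group effect = (d₁ + d₂ + d₃)/4 = 0.75 × mean of the three follow-up differences.

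For a constant 0.40 SD this is 0.75 × 0.40 = 0.30 SD. In simulation (2000 trials per setting) the ratio was 0.7500 in every data set.

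**Step 2: the test.** The residual of the four-level mean is 3/4 of the residual of the follow-up mean, so the standard error shrinks by the same factor. The t statistics agreed to within 1e-14. At correlation 0.5 and a constant 0.40 SD, power was 0.737 in both versions. Under no effect, rejection was 0.052 in both.

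**Step 3: against the primary time point.** The factor 3/4 is relative to the mean of the follow-ups, not to discharge. With effects of 0.5, 0.3 and 0.1 SD:

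- discharge effect: 0.50
- mean of follow-ups: 0.90/3 = 0.30
- four-level coefficient: 0.90/4 = 0.225

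The simulated values were 0.220 for the four-level coefficient and 0.494 at discharge, a reduction of 55%. Most of that comes from averaging over the later visits (0.50 to 0.30); the baseline level adds the step from 0.30 to 0.225.

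**Step 4: where the dilution comes from.** Without the covariate, the four-level group main effect was 0.297 for a true 0.40, which is also about 3/4. Counting baseline as an outcome level causes the dilution. The covariate turns an average of 3/4 into exactly 3/4 in every data set.

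**Step 5: group-by-time.** With a covariate-by-time term, the contrast of follow-up k against baseline is d_k − 0 = d_k, which is not biased. Power of the Greenhouse-Geisser test for a constant 0.40 SD:

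| Correlation | Without covariate | With covariate |
|---|---|---|
| 0.3 | 0.277 | 0.310 |
| 0.5 | 0.386 | 0.437 |
| 0.7 | 0.589 | 0.633 |
| 0.85 | 0.894 | 0.910 |

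The largest shortfall in any setting was 0.004 (0.985 against 0.989), where power is near 1. Without a covariate-by-time term, a covariate that is constant within a patient leaves the balanced within-subject contrasts unchanged.

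**The case against.** The strongest reply is that no inference is damaged. The ANCOVA is additional to the main ANOVA, the group test keeps its p-value, and in a design with a pre-intervention level the training effect is ordinarily read from group-by-time. The effect size and the change-score comparisons are defined separately and are untouched. The bracket listing baseline is attached to the ANOVA, and the covariates are introduced only as examples. All of this stands and lowers the weight of the point. It does not remove it: the second model is also called repeated measures, its time factor is not redefined, and no term is named as the adjusted effect, so the diluted coefficient remains open to being reported.

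Three stronger readings are tempting, and the documents do not support them.

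- **That the double use costs power in group-by-time.** It does not; power with the covariate is the same or slightly higher. The 3-df interaction is weaker than a 1-df group test on the follow-ups when the effect is constant (0.437 against 0.737 at correlation 0.5), but that gap is there without the covariate too (0.386). With 0.5 SD at discharge only, the order reverses (0.610 against 0.192).
- **That the primary effect is shrunk by one quarter.** The factor applies to the group main effect against the follow-up mean. Against discharge it equals one quarter only if the discharge difference equals that mean, as with a constant effect.
- **That the HADS analysis has the same fault.** The article does not say which visit's psychiatric score is the covariate, or that it enters the model for the HADS itself. The fault follows only if both hold with the baseline score.

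**Conclusion.** The point holds as one of estimation and wording. Read as written, the adjusted model has the preoperative score on both sides, and its group main effect, like the difference in adjusted group means, is exactly 3/4 of the mean adjusted follow-up difference. That result is algebraic: it needs four levels and the same patients and covariates in both models, and it does not depend on the correlation or the effect size. The shortfall against the discharge effect does depend on the pattern over time: 25% for a constant effect, 55% for the assumed 0.5/0.3/0.1 SD. There is no false-positive risk and no loss of power from the covariate. Because the model is supplementary and the affected term is not named as the training effect, the severity is minor to moderate.

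**What to change.** In the ANCOVA, restrict the repeated outcome levels to discharge, 3 months and 12 months. Keep the preoperative score of the same test as covariate and include group-by-visit. Report the baseline-adjusted group contrast at discharge as the adjusted training effect, with the 3- and 12-month contrasts as secondary. If the baseline HADS score is meant as a covariate in the HADS model, apply the same rule there, and state which visit the psychiatric covariates come from.

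Keeping baseline as a level and only removing the covariate is not enough, because the group main effect stays diluted (0.297 for a true 0.40).

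The discharge contrast matches the primary outcome and is more efficient than the change-score t test: with 0.5 SD at discharge, 37 per group and an assumed correlation of 0.5, simulated power was 0.670 against 0.547. The cost is one sentence in the analysis section; no data and no patients are added.

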### Neuropsychological assessment

A battery of cognitive tests will be performed by a neuropsychologist on the day before surgery, at discharge from rehabilitation, and at 3 and 12 months after discharge. When available, parallel test forms will be used at follow up to account for learning effects. The order in which the parallel test forms are presented will be counterbalanced so that each parallel test form occurs with the same frequency at each test time point.

The cognitive test battery assesses selective attention, verbal and visual memory with short-delay and long-delay episodic memory conditions, verbal working memory, cognitive flexibility, word fluency and symbol processing. Selective attention will be examined using the Trail Making Test A (TMT-A) [20] and the *Alterskonzentrationstest* (AKT) [21]. In the TMT-A, the patient has to link numbers in ascending order on a test sheet. The AKT consists of a matrix of similar visual stimuli, where a target stimulus has to be marked.

To assess verbal memory, the *Verbaler Lern- und Merkfähigkeitstest* (VLMT), a modified German version of the Rey Auditory Verbal Learning Test [22], will be applied. This test can be used to evaluate short-term memory, learning, episodic memory, and verbal discriminability. First, the patient has to concentrate on a word list that is read out loud by the investigator. The direct retrieval of the patient is scored as short-term memory performance. Second, the patient has to learn the word list in five learning trials. The sum of the recalled words represents a learning parameter. Third, a second word list with new words is presented verbally only once, to divert attention from the first word list. After this, the learned words of the first word list have to be recalled; this is used as a measurement of a short-delayed function of verbal episodic memory. A second verbal episodic memory measurement is performed 20 min later (long delay). Finally, the verbal recognition ability is proven by discriminating between already learned and new words. Between the short-delayed verbal episodic memory trial and the long-delayed verbal episodic memory trial, nonverbal cognitive tests are performed to avoid the potential effect of interfering words not included in the learned wordlist.

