### Power and sample size estimation

Cognitive training for patients undergoing heart surgery administered by de Tournay-Jette et al. (2012) [19] revealed medium-to-large effect sizes (*η*^2^ = 0.10–0.23). We have decided to use the smaller effect size (*η*^2^ = 0.10) for calculation so as not to underestimate the required sample size. Using this effect size, 37 patients per group are needed to obtain statistical power of 80% at a significance level of *p* = 0.05 (two-tailed). Based on previous cardiosurgical studies, we estimate a dropout rate of 20% between each of the four assessment time points. Thus, the number of study patients recruited at baseline assessment was fixed at 72 patients per group. For sample size and statistical power calculations, we used G*Power-3 analysis software.

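### At discharge, the main training-effect contrast and the reported effect size rest on raw pre-post change; adjusting for the preoperative score would be more precise at almost no cost

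*Protocol article*

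**What the plan says.** The primary outcome is the training effect on the objective cognitive tests at discharge from rehabilitation (Protocol article, Primary outcome measure). Under Neuropsychological assessment, baseline testing is fixed: "A battery of cognitive tests will be performed by a neuropsychologist on the day before surgery". A preoperative score on each test is therefore part of the design for every patient.

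Planned statistical analyses then sets out four things that bear on this point:

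- The main analysis is a group by time repeated measures ANOVA in which baseline is one level of the time factor, so it is an outcome and not a covariate.
- An additional repeated measures ANCOVA is meant to check for confounders. Preoperative cognitive values are one example in its covariate list, beside age, sex, education, psychiatric scores and perioperative variables.
- Between-group t tests, labelled post hoc and explorative, use post minus pre scores: "The change in cognitive values is the dependent variable, and the treatment group (cognitive training group/control group) is the independent variable". The Mann-Whitney fallback uses the same change scores.
- The reported effect size is also a difference of changes: "Effect size of the cognitive training will be calculated by the difference in the pretest-posttest measure between the intervention and control group". It is divided by the pooled pretest SD.

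**The concern.** A change score fixes the slope of the follow-up score on the preoperative score at 1. With equal SDs at the two visits, the actual slope is the correlation r, which is below 1 for any imperfectly reliable test. Forcing it to 1 has two consequences. It adds variance to the group difference, and it over-corrects chance baseline differences: an arm that happens to start higher is expected to gain less, and that shows up as part of the training effect.

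The choice reaches beyond the exploratory t test. With two time points, the group by time test of the ANOVA is the change-score t test (F = t²). With all four visits in the model the omnibus interaction is a different test, but its baseline-to-discharge contrast still compares the same mean changes. The effect size carries no exploratory label and is the only definition of the size of the training effect that the article gives. At stake is precision on a broad test battery under false discovery rate control, and an avoidable source of error in the headline estimate.

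**Working it through.** **Inputs from the article (Power and sample size estimation).** Eta-squared 0.10; "37 patients per group are needed to obtain statistical power of 80"%; two-sided alpha 0.05; on dropout, "we estimate a dropout rate of 20% between each of the four assessment time points"; and "the number of study patients recruited at baseline assessment was fixed at 72 patients per group".

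**Assumptions, not in the article.** Pre-post correlation r = 0.5 to 0.8; equal SDs at the two visits; eta-squared 0.10 read as the effect on the change-score scale.

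**Reproducing the plan's figures.** f = √(0.10/0.90) = 0.333, so d = 2f = 0.667. The noncentral t gives power 79.7% at 36 per arm and 80.8% at 37, so 37 reproduces. Three intervals at 80% retention give 0.8³ = 0.512, and 37/0.512 = 72.3, against 72 stated. Expected at discharge: 72 × 0.8 = 57.6, about 58 per arm.

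**Variance.** With equal SDs (scaled to 1), the variance of the group difference is proportional to 2(1-r) for change scores and to 1-r² after baseline adjustment. The ratio is 2/(1+r).

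| r | change | adjusted | ratio | excess |
|---|---|---|---|---|
| 0.5 | 1.00 | 0.75 | 1.33 | 33% |
| 0.6 | 0.80 | 0.64 | 1.25 | 25% |
| 0.7 | 0.60 | 0.51 | 1.18 | 18% |
| 0.8 | 0.40 | 0.36 | 1.11 | 11% |
| 0.9 | 0.20 | 0.19 | 1.05 | 5% |

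A simulation with 58 per arm and 20,000 replicates gave ratios of 1.34 (r = 0.5) and 1.10 (r = 0.8).

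**Unequal SDs.** Let k be the follow-up SD divided by the baseline SD. The ratio becomes (1 + k² - 2rk) / (k²(1-r²)). At r = 0.8 and k = 1.1 it is 0.450/0.4356 = 1.03. At k = 1.25 it is 0.5625/0.5625 = 1.00, because the true slope rk is then exactly 1. The numerator exceeds the denominator by (1-rk)², so apart from the one degree of freedom adjustment does not lose.

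**Power per test**, using d/√((1+r)/2) for the adjusted analysis:

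| effect, n per arm | change | adjusted, r = 0.8 | adjusted, r = 0.5 |
|---|---|---|---|
| d = 0.667, 37 | 80.8% | 84.7% | 90.4% |
| d = 0.667, 58 | 94.5% | 96.4% | 98.4% |
| d = 0.5, 58 | 76.1% | 80.4% | 86.9% |

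**Chance imbalance.** At 58 per arm the baseline difference between arms has SD √(2/58) = 0.186 score SDs. Multiplied by (1-r), this leaves a typical error of 0.093 SD (r = 0.5) to 0.037 SD (r = 0.8) in the change-score estimate. In the simulation the change-score estimate moved by -0.50 and -0.20 per unit of imbalance at r = 0.5 and 0.8; the adjusted estimate moved by about 0.

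**The case against.** The strongest reply is that the article already plans baseline adjustment. A reader of the t-test sentence alone might infer that the training effect is never adjusted; the additional ANCOVA rules that out. If its software lets the covariate interact with time, its baseline-to-discharge contrast gives a baseline-adjusted difference, because regressing change on group and baseline yields the same group coefficient as regressing the follow-up score on them. This part of the reply stands. What it leaves open is status and clarity. The ANCOVA is an extra confounder check, its covariate list is illustrative, it appears to keep baseline as an outcome level while also using it as a covariate, and the effect size is not drawn from it.

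Second, the quoted t test is only exploratory. That is true, but the main ANOVA's discharge contrast and the effect size rest on the same change.

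Third, change-score analysis is valid under randomization, and the article justifies its effect-size metric by a cited source. Both are accepted. A reader might infer bias, but over repeated randomization there is none. The pooled pretest SD can stay as the divisor; only the numerator is at issue.

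Fourth, the gain at discharge is small if the planned effect is true, since power is already 94.5%. This also stands. A reader might infer that the sample size is wrong or the trial underpowered; the calculation does not show that.

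**Conclusion.** The point holds as an improvement in efficiency, not as an error or a bias. For the primary time point, the main contrast and the reported effect size use unadjusted change although the covariate is collected on every patient.

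The size depends on figures the article does not give. The excess variance of 33% to 11% requires r between 0.5 and 0.8 and equal SDs. It is about 5% at r = 0.9, and at r = 0.8 a follow-up SD 1.1 times the baseline SD cuts it to 3%. So 11% is not a floor, and the range should not be read as a property of this trial.

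The power gain is 2 to 4 points at the planned effect with 58 per arm, 4 to 10 points at 37 per arm, and 4 to 11 points at 58 per arm if the true effect is d = 0.5. The last case is the most relevant, because lost precision matters most when the effect is smaller than planned.

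**What to change.** For each cognitive test, name as the main discharge comparison a linear model with the discharge score as outcome and group plus the preoperative score of the same test as the only terms. Baseline should not also be an outcome level. Report the adjusted group difference with its 95% CI, fit the model in each imputed data set and pool the results. For the effect size, divide the pooled adjusted difference by the pooled pretest SD that the article already names. Change-score tests can stay as supportive analyses, and the additional ANCOVA with further covariates as a sensitivity check.

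The change is to wording only: no new data, visits or patients, and no revision of the sample size. The cost is one degree of freedom per model and an assumed linear relation between the discharge and preoperative scores.
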